## **5.4 TIME POINTS AND VISIT WINDOWS**

For the statistical analysis summarized by visit, only the scheduled visit was used.

- **Use of data from unscheduled visits:**

Unscheduled visit data will be used for baseline value. The unscheduled visit data of laboratory tests, vital signs, ECG and other safety indicators are not used for by-visit summary analysis, but should be included for last visit and worst value record (PCSA abnormal value).

## **6 Statistical Analysis Methods**

### **6.1 GENERAL PRINCIPLES**

All statistical analyses will be performed using SAS 9.4 (or later version). This trial is mainly based on descriptive statistics, and in principle, no comparison will be made.

All data collected in this study will be presented in data listings and summarized in tables by treatment group, unless otherwise specified. Subjects receiving placebo in different cohorts will be combined and analyzed in summary tables.

Categorical data were presented as frequency (percentage). Unless otherwise specified, the number of subjects in each treatment group in the corresponding study population will be the denominator for the percentages. Percentages will be displayed to 1 decimal place.

Continuous data will be shown as mean  $\pm$  standard deviation or median (minimum, maximum). The mean and median will be displayed to 1 more decimal place than the original data, the standard deviation will be displayed to 2 more decimal places than the original data, and the maximum and minimum values will be displayed to the same decimal place as the original data. For PK parameters, geometric means and coefficients of variation will be displayed to the first decimal place, unless otherwise specified.

Baseline value: defined as the last available measurement prior to receiving the first dose of study treatment.

The following notation will be used in the tables of statistical analysis:

| Treatment Group in Protocol                                   | Treatment Groups in Statistical Analysis |
|----------------------------------------------------------------------|-------------------------------------------------|
| Cohort 1, treated with IBI362                                 | IBI362 – Cohort 1                               |
| Cohort 2, treated with IBI362                                 | IBI362 – Cohort 2                               |
| Cohort 3, treated with IBI362                                 | IBI362 – Cohort 3                               |
| Cohort 1, Cohort 2, Cohort 3, Placebo Treated                 | Placebo                                         |
| Cohort 1, Cohort 2, Cohort 3, treated with dulaglutide 1.5 mg | Dulaglutide 1.5 mg                              |

## 6.2 SUBJECT DISPOSITION

- **Subject Disposition**

Summary of subject disposition will include the following information:

- Number of subject screened and reasons for screen failure
- The number and percentage of subjects who were randomized, treated, prematurely discontinued study drug, and prematurely discontinued from the study. Subjects who withdrew early from the study will be listed.

Premature discontinuation of study drug is defined as failure to receive the last scheduled dose of study drug.

- The number and percentage of subjects in each analysis population (ie, safety analysis set, efficacy analysis set, PK analysis set, PD analysis set, and antidrug antibody analysis set) will be summarized by treatment group. The inclusion or exclusion of each subject from the analysis population and the reason for exclusion will be presented in the listings.
- **Protocol Deviations**

In the safety analysis set, the number and percentage of subjects with major protocol deviations during the study will be summarized by treatment group and type of protocol deviation, and subjects with protocol deviations will be listed along with their detail description.

## **6.3 DEMOGRAPHIC AND OTHER BASELINE CHARACTERISTICS**

### **6.3.1 Demographic and Baseline Characteristics**

Descriptive statistics for demographic data and baseline characteristics will be summarized by treatment group in the safety analysis set.

The following continuous variables will be summarized using number of cases, mean, standard deviation, median, Q1 and Q3, minimum and maximum:

- Age (years) = (date of informed consent – date of birth + 1)/365.25, rounded off at the lowest integer;
- Height (cm)
- Weight (kg)
- Body mass index (kg/m^2)
- Waist circumference (cm)
- Fasting plasma glucose (mmol/L)
- Total cholesterol (mmol/L)
- Triglycerides (mmol/L)
- Low-density lipoprotein (mmol/L)
- High density lipoprotein (mmol/L)
- Glycosylated hemoglobin (%)
- Alanine aminotransferase (ALT) (IU/L)
- Aspartate aminotransferase (AST) (IU/L)
- Duration of T2DM history (year) = (date of informed consent – date of T2DM diagnosis + 1)/365.25

The number and percentage of subjects will be summarized for the following categorical variables:

- Gender: Male, Female
- Ethnicity: Asian, Other
- Ethnic group: Han, others
- Main method of glycemic control in the previous two months: lifestyle intervention, stable dose of metformin therapy

Other efficacy variables with baseline measurements (insulin, fasting C-peptide, OXM, GLP-1, etc.) and safety variables (laboratory tests, vital signs, ECG, etc.) will be analyzed together with post-baseline measurements in the relevant sections.

Demographic data and baseline characteristics of subjects will be listed.

### **6.3.2 Medical History**

- **Disease History**

Descriptive statistics for history of diagnosis of the study disease were summarized by treatment group in the safety analysis set.

The following continuous variables were summarized by number of cases, mean, standard deviation, median, Q1, Q3, minimum, and maximum:

- Time on T2DM with medical history (years) = (Date of informed consent – Date of diagnosis of T2DM + 1)/365.25

Incomplete dates of diagnosis of type 2 diabetes were imputed according to rules in Section 5.3.

The number and percentage of subjects will be summarized for the following categorical variables:

- Glycemic control methods in the previous two months

A summary of study disease history was presented in the subject's baseline characteristics table.

Subjects' medical history of type 2 diabetes was tabulated.

- **History of non-study disease**

The MedDRA dictionary (version 24.0 or later) will be used to code the preferred term (PT) and system organ class (SOC), respectively, for medical history including surgical history. In the safety analysis set, the number and percentage of subjects with a medical history will be summarized by treatment group, SOC and PT. If a subject had multiple medical or allergy histories in the same SOC or PT category, the subject will be counted only once in that SOC and PT category.

The history of the disease under study and the history of non-study diseases will be listed.

### **6.3.3 Prior/Concomitant Therapy**

- **Prior/concomitant medications**

The WHO-DD Dictionary (Version March 2021 or newer) will be used to code the Anatomical Therapeutic Chemical (ATC) Level 1-4 terms for prior/concomitant medications and the medication name (PN), respectively. In the safety analysis set, the number and percentage of subjects with prior/concomitant medications will be summarized by ATC level 2, ATC level 4, and PN as well as by treatment group. If a subject had multiple prior/concomitant medications in the same ATC Level 2, ATC Level 4, or PN category, the subject will be counted only once in that ATC Level 2, ATC Level 4, or PN category.

Prior medications are defined as medications that have started before receiving the first dose of study treatment and that have stopped before receiving the first dose of study treatment.

Concomitant medication is defined as medications that were taken from the day of the first dose of study treatment through 56 days after the last dose of study treatment, including medications that started before the first study treatment and were ongoing after the first study treatment, and medications that started from the day of the first study treatment through 56 days after the last dose.

- **Prior/Concomitant Non-Drug Therapies**

The MedDRA dictionary (version 24.0 or later) will be used to code the preferred term (PT) and system organ class (SOC) for prior and concomitant non-drug therapies, respectively. In the safety analysis set, the number and percentage of subjects with prior and concomitant non-drug therapies will be summarized by treatment group, SOC and PT. If a subject had multiple prior and concomitant non-drug therapies in the same SOC or PT category, the subject will be counted only once in that SOC and PT category.

Prior non-drug therapy is defined as receiving a non-drug therapy that had started before the first dose of study treatment and had stopped before the first dose of study treatment.

Concomitant non-drug therapy is defined as non-drug therapy that started or was continuing from the day of first dose of study treatment through 56 days after the last dose, including those that started before the first dose of study treatment and were continuing after the first dose of study treatment, and those that started from the day of first dose of study treatment through 56 days after the last dose.

Prior/concomitant medications and non-drug therapies will be tabulated.

## **6.4 EXTENT OF STUDY DRUG EXPOSURE AND COMPLIANCE**

The extent of exposure to study drug was assessed and summarized in the safety analysis set.

### **6.4.1 Extent of Study Drug Exposure**

Assessments of the extent of exposure to study drug include cumulative exposure to study drug, relative dose intensity and weeks of exposure.

Cumulative exposure, relative dose intensity and weeks of exposure to study drug will be summarized by treatment group with the following statistics: number of subjects, mean, standard deviation, median, Q1, Q3, minimum, and maximum.

Relative dose intensity (%) = (cumulative drug exposure/ total planned dose) × 100%, the total planned dose is the sum of the planned doses administered throughout the treatment period.

Exposure weeks are calculated as (date of last dose – date of first dose + 7 days)/7 days.

Exposure of study treatment will be listed.

## **6.5 EFFICACY ANALYSIS**

Unless otherwise specified, the analysis of HbA1c will be performed in the efficacy analysis set, the efficacy analysis of PD parameters will be performed in the PD analysis set, and the analysis of other efficacy indicators will be performed in the safety analysis set.

### **6.5.1 Analysis of HbA1c/fasting blood glucose/body weight/waist circumference/BMI**

Baseline and different post-baseline visits were descriptively analyzed by treatment group (Week 5, Week 9 and Week 13) for the following efficacy measures: HbA1c, fasting blood glucose, body weight, waist circumference, and BMI and their change values from baseline, and the mean values of HbA1c and fasting blood glucose and their change from baseline over time will be plotted. Percent change from baseline over time will be plotted for body weight. Change from baseline over time will be plotted for waist circumference and BMI.

For HbA1c and fasting blood glucose, a mixed model repeated measures (MMRM) model with baseline variables will be used to calculate the point estimate and 90% confidence interval of the change from baseline after treatment, and the point estimate and 90% confidence interval of the difference between each IBI362 cohort and placebo. Nominal p-values for comparisons are provided. The SAS program for the MMRM model references the following:

**Proc mixed data = indata;**

```

Class treatment (ref ="placebo") usubjid time;

Model chg = base treatment time treatmenttime/solution;

Repeated time/type = un sub = usubjid (treatment) rcorr;

Lsmeans treamenttime/diff = all alpha = 0.1;

Ods output lsmeans = datm diffs = datd;

```

### **Run;**

Where treatment is the treatment group, time is each visit, chg is the change from baseline of analysis indicators, and base is the corresponding baseline value. The unstructured correlation was used to estimate the correlation coefficient matrix of change from baseline at each visit for each subject in the MMRM model. The likelihood of the model was constructed using the REML method (SAS proc mixed default likelihood method).

If necessary, MMRM model will be used to estimate the point estimate and 90% confidence interval of each treatment group, and the point estimate and 90% confidence interval of the difference between each IBI362 treatment group/polaglutide group and placebo for other repeated measures efficacy endpoints. Nominal p-values are provided for comparisons.

Results were tabulated.

### **6.5.2 Analysis of fasting insulin/fasting c-peptide/lipid profile/blood pressure/HOMA-β/HOMA-IR/fasting endogenous OXM/fasting endogenous GLP-1**

The following efficacy indicators after baseline and at D85 visit were descriptively analyzed by treatment group: fasting insulin, fasting c-peptide, blood lipids (triglycerides, total cholesterol, low-density cholesterol and high-density cholesterol), blood pressure (systolic blood pressure, diastolic blood pressure), HOMA-β, HOMA-IR, fasting endogenous OXM and fasting endogenous GLP-1 and their changes from baseline.

If necessary, ANCOVA model will be used to calculate the point estimate and 90% confidence interval of each treatment group and the point estimate and 90% confidence interval of the difference between each IBI362 treatment group/dulaglutide group and placebo. Missing values will be imputed using LOCF in the ANCOVA model and the nominal p-values for the comparisons were provided.

The SAS program for the ANCOVA model can be found at:

```
Proc mixed data = indata method = type3;
```

```
Class treatment (ref ="placebo");
```

Model chg = base treatment;

Lsmeans treatment/diff = control ("placebo") alpha = 0.1;

Ods output lsmeans = datmean diffs = datdiff;

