### 2.2.2 Secondary endpoints

- To evaluate the pharmacokinetic parameters of IBI362 in patients with type 2 diabetes, including but not limited to: time to maximum concentration ( $T_{max}$ ), maximum concentration ( $C_{max}$ ), area under the curve (AUC), volume of distribution (Vd), half-life ( $T_{1/2}$ ), clearance (CL), accumulation ratio (AR), etc.;
- To assess the pharmacodynamics parameters of IBI362 after multiple doses: changes of fasting blood glucose, glucagon, insulin, fasting C-peptide, hemoglobin A1c (HbA1c), oxytomodulin (OXM) and GLP-1 after administration;
- Changes of fasting blood glucose, insulin and glucagon at steady state in each dose level during dose escalation;
- Changes from baseline in each parameter of MTT test after multiple dose administration;
- Changes of self-measure blood glucose after multiple doses;
- The incidence of anti-IBI362 antibody (ADA) and neutralizing antibody (NAb) in serum before and after administration

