#### 9.4.5 Analysis of kinetic and pharmacodynamic parameters

Each PK parameter, including but not limited to  $T_{max}$ ,  $C_{max}$ , area under the curve (AUC), volume of distribution (Vd), half-life ( $T_{1/2}$ ), clearance (CL), and accumulation coefficient (AR), will be summarized for each dose cohorts separately.

Pharmacodynamics parameters will be summarized, including: fasting blood glucose, glucagon, insulin, fasting C-peptide, HbA1c, endogenous OXM, and GLP-1 measurements at baseline and at various time points after drug administration, and changes from baseline at each time point will be summarized.

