#### 9.4.6 Exploratory Analysis

Changes from baseline in HOMA-Beta, HOMA-IR, weight in fasting, waist circumference, and BMI will be summarized at each time point after treatment.

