#### **3.4 PHARMACODYNAMIC PARAMETERS**

- To assess the pharmacodynamic parameters of IBI362 after multiple doses: changes in fasting blood glucose, insulin, fasting C-peptide, HbA1c, endogenous OXM and GLP-1 before and after administration;
- Changes in fasting blood glucose and insulin at steady state in each dose phase during dose escalation;
- The change of each parameter of MTT test from baseline after multiple dose administration;

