### **6.6.3 Vital Signs**

Vital signs (including body temperature, pulse and respiratory rate) and their changes from baseline will be listed and summarized by visit. Worst results for potentially clinically significant postbaseline vital signs will be summarized according to the PCSA criteria in Appendix 1.

Vital sign results will be listed.

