## **6.9 ANALYSIS OF PHARMACODYNAMIC PARAMETERS**

Pharmacodynamic measures include HbA1c, fasting c-peptide, fasting plasma glucose, insulin, OXM, and GLP-1. Relevant analyses are described in the efficacy analysis sections 6.5.1 and 6.5.2.

Pharmacodynamic test results will be listed.

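### SAP 6.5.2 commits to a fasting insulin summary for only the last of three dose phases, although the per-phase insulin endpoint is kept and the D29 and D57 samples are drawn

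*Combined protocol and SAP*

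**What the plan says.** Protocol 2.2.2 lists as a secondary endpoint "Changes of fasting blood glucose, insulin and glucagon at steady state in each dose level during dose escalation". The change table in SAP 2.5.2 edits this endpoint and removes only glucagon, for lack of data. SAP 3.4 accordingly carries "Changes in fasting blood glucose and insulin at steady state in each dose phase during dose escalation".

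The two halves of that endpoint are analysed in different places. Fasting glucose is in SAP 6.5.1: "Baseline and different post-baseline visits were descriptively analyzed by treatment group (Week 5, Week 9 and Week 13) for the following efficacy measures". Fasting insulin is in SAP 6.5.2: "The following efficacy indicators after baseline and at D85 visit were descriptively analyzed by treatment group: fasting insulin", followed by C-peptide, lipids, blood pressure, HOMA-β, HOMA-IR, OXM and GLP-1. SAP 6.9, on pharmacodynamic parameters, says only that "Relevant analyses are described in the efficacy analysis sections 6.5.1 and 6.5.2", and adds a listing of results.

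The protocol was broader. For insulin, C-peptide, OXM and GLP-1, section 9.4.5 states that "changes from baseline at each time point will be summarized". For HOMA, section 9.4.6 states that changes "will be summarized at each time point after treatment".

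**The concern.** The endpoint asks for insulin phase by phase, but the section that analyses insulin names one post-baseline visit, in the last phase. Followed as written, the tables would show fasting glucose at each dose level of the escalation and fasting insulin only at the maintenance dose. The two could not be read side by side in the first two phases, which is the purpose of a joint per-phase endpoint. The narrowing from the protocol is also undeclared: SAP 2.5.2 records the loss of glucagon and the change of model, interval level and analysis sets, but says nothing about fewer visits.

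**Working it through.** The point involves no power, alpha or sample-size figure. The check is a count of dose phases against samples and named visits.

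Inputs:
- Three four-week phases per cohort: protocol Synopsis and Table 1.
- Post-baseline fasting PD samples at D3, D8, D29, D57, D78 and D85, with insulin in the panel: protocol 7.3.2 and the notes to Table 3.
- Weeks 5, 9 and 13 correspond to D29, D57 and D85: protocol Table 2.
- Visits analysed: SAP 6.5.1 and 6.5.2.

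| Phase | Days | Dose, Cohorts 1 / 2 / 3 (mg) | Sample closing the phase | Glucose, SAP 6.5.1 | Insulin, SAP 6.5.2 |
|---|---|---|---|---|---|
| 1 | D1–D28 | 1.0 / 1.5 / 2.0 | D29, pre-dose | Week 5 | not named |
| 2 | D29–D56 | 2.0 / 3.0 / 4.0 | D57, pre-dose | Week 9 | not named |
| 3 | D57–D84 | 3.0 / 4.5 / 6.0 | D85, 168 h after the D78 dose | Week 13 | D85 |

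Results:
- Glucose: 3 of 3 phases. Insulin: 1 of 3 phases, so 3 − 1 = 2 phases lack a named summary.
- Across cohorts there are 3 × 3 = 9 cohort-by-phase cells. Insulin is named for 3 × 1 = 3 and not for 9 − 3 = 6.
- In planned values, 8 IBI362 patients × 3 cohorts × 2 visits = 48 scheduled fasting insulin results on IBI362. Over all 42 patients the figure is 42 × 2 = 84.
- With the 6.5.1 visits applied to insulin, coverage becomes 3 of 3 phases and 9 of 9 cells.

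The reading of 6.5.2 has to be argued, because its visit phrase is not clean. Taken literally, the reference to a time after baseline, together with D85, could admit other post-baseline visits. Three things favour baseline and D85 only:
1. SAP 6.5.1 lists its three visits explicitly, so the author named visits where several were meant.
2. SAP 6.5.3 and 6.5.4 use a parallel two-occasion form: baseline and D85 for the seven-point profile, baseline and D80 for the meal test.
3. The ANCOVA model in 6.5.2 has a baseline and a treatment term but no visit term, unlike the MMRM in 6.5.1.

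Supplementary Fig. S4, which shows HOMA change at week 12 only, fits the same reading.

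**The case against.** The strongest reply is that the data are not lost and that other parts of the SAP may reach them. SAP 6.1 summarises all collected data in tables by treatment group as a default. SAP 6.9 lists every PD result. SAP 6.5.1 allows an MMRM for other repeated-measures endpoints. SAP 6.5.4 summarises the meal test at D80, whose first test point is fasting and includes insulin. The trial is also descriptive, with eight IBI362 patients per cohort.

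All of this is true, but none of it commits to a summary at D29 or D57. The 6.1 default gives way where something else is specified, and 6.5.2 does specify. A listing is not a summary of change by phase. The MMRM is to be run only if needed. D80 falls in phase 3, which D85 already covers. What stands is that the wording is ambiguous and the consequence is limited to a descriptive secondary endpoint.

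A reader might infer three stronger things that the documents do not support:
- That the per-phase insulin endpoint goes wholly unreported. It does not: D85 closes the maintenance phase and is analysed.
- That the gap in this endpoint is five of the six post-baseline samples. D3 and D8 follow the first dose and are not end-of-phase values, and D78 lies in the same phase as D85. The endpoint gap is two samples.
- That blood pressure is examined only at D85, away from peak exposure. SAP 6.6.3 reads "Vital signs (including body temperature, pulse and respiratory rate) and their changes from baseline will be listed and summarized by visit". Its bracketed list is introduced as an inclusion and need not be complete, and SAP 3.1 counts blood pressure among the vital signs. Appendix 1 sets systolic and diastolic criteria, against which worst post-baseline values are summarised. An argument from Tmax would also rest on Supplementary Table S1, which covers the first dose only.

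**Conclusion.** The concern holds in a limited form. The insulin half of a retained secondary endpoint has no committed summary for dose phases 1 and 2 (D29 and D57), while the glucose half is summarised for all three phases. For C-peptide, OXM, GLP-1, HOMA-β and HOMA-IR, which the endpoint does not include, the fault is an unrecorded departure from protocol 9.4.5 and 9.4.6.

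This rests on three assumptions. First, 6.5.2 means baseline and D85; if it means more, the sentence still needs rewording, because it does not say which visits. Second, the sample closing each phase represents steady state, since the documents do not name the sample that does. Third, patients follow the planned escalation; the Cohort 2 backup schedules would change which dose a visit represents. The change should be made, but the gap does not touch the primary safety assessment.

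**What to change.** In SAP 6.5.2, name D29, D57 and D85 (Weeks 5, 9 and 13, as in 6.5.1) for fasting insulin and its change from baseline, and replace the ambiguous visit phrase with that list. Apply the same visits to C-peptide, OXM, GLP-1, HOMA-β and HOMA-IR, or record the reduction and its reason in SAP 2.5.2. Because the protocol text covers every time point, 2.5.2 should also say whether D3, D8 and D78 are to be tabulated. As a minor clarification, name systolic and diastolic blood pressure in the by-visit summary of SAP 6.6.3.

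The cost is SAP wording and a few table columns (two more visits per measure). All samples are already scheduled.

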14. Blood samples for HbA1c will be collected at screening, within 1 h prior to dosing on D1 of Week 1, within 1 h prior to dosing on D29 of Week 5, within 1 h prior to dosing on D57 of Week 9, and at 168 h  $\pm$  12 h (D85) after dosing on D78 of Week 12. If a patient fails to complete the study and withdraws from the study prematurely, samples will be collected at the early termination visit. Two (2) mL will be collected at each collection point and the detailed procedures will be described in the central laboratory manual.
15. Immunogenicity sample will be collected in Week 1 (within 1 hour before the start of infusion), Week 5 (within 1 hour before infusion on D29), Week 9 (within 1 hour before infusion on D57), Week 13 (168 hours  $\pm$  12 hours after Week 12 administration) and safety follow-up visit. If a patient withdraws prematurely. An immunogenicity sample should also be collected at early termination visit as far as possible. Collect 5 mL at each blood collection point. Refer to the central laboratory manual for the detailed operation process.
16. The PK/PD sampling points are detailed in Table 3.
  - Central laboratory test.

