| 
All efficacy analyses were performed on the efficacy analysis set. Efficacy endpoints will be analyzed only descriptively. For continuous efficacy endpoint indicators, the corresponding means and 95% confidence intervals will be calculated for IBI362 subjects in each dose group, all placebo subjects and all active control subjects, respectively. A two-sample t-test will be used to calculate the p-value of IBI362 versus placebo for each dose group and provide the corresponding point estimate and 95% confidence interval of the difference. LOCF missing values will be used for imputation. For the categorical efficacy endpoints, the ratio within each dose group will be calculated and the 95% confidence interval within the group will be calculated using Clopper-Pearson; the difference between IBI362 placebo groups will be compared using the chi-square test and the corresponding 95% confidence interval will be calculated. Missing values for grouped endpoints will be imputed using the default non-response method.
 | 
Analysis of HbA1c was performed in the efficacy analysis set, analysis of pharmacodynamic parameters was performed in the PD analysis set, and other efficacy endpoint indicators were performed in the safety analysis set unless otherwise specified. For continuous efficacy endpoint indicators, mixed model repeated measures (MMRM)/ANCOVA model was used to estimate the point estimate and 90% confidence interval of each treatment group, and the point estimate and 90% confidence interval of the difference between each IBI362 treatment group/dulaglutide group and placebo. LOCF missing values will be used for imputation. Nominal p-values are provided for comparisons. No multiplicity adjustment will be made in this trial.
 | 
The primary endpoints of this trial are safety and tolerability. The number of subjects in each treatment group is small. 90% confidence interval will be provided. No multiplicity adjustment will be made. Only nominal p value will be provided.
 |

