## **5 Data processing**

### **5.1 GENERAL SPECIFICATIONS**

### **5.2 EFFICACY DATA HANDLING PRACTICES**

In this trial, efficacy data will be analyzed as it is and, if not otherwise specified, missing values will not be imputed.

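### LOCF in SAP 6.5.2, and its blanket mention in SAP 2.5.2, would report lower-dose values as target-dose D85 results in a titration trial

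*Combined protocol and SAP*

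**What the plan says.** The SAP deals with missing efficacy values in four places.

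- **SAP 5.2** sets the default: "if not otherwise specified, missing values will not be imputed".
- **SAP 6.5.1** covers the main glycaemic measures: "For HbA1c and fasting blood glucose, a mixed model repeated measures (MMRM) model with baseline variables will be used". The model is fitted by REML with an unstructured covariance, and no imputation is mentioned. The same section allows this MMRM for other repeatedly measured efficacy endpoints, without saying when.
- **SAP 6.5.2** covers fasting insulin, C-peptide, OXM and GLP-1, lipids, blood pressure, HOMA-β and HOMA-IR at D85. The analysis is conditional: "If necessary, ANCOVA model will be used to calculate the point estimate and 90% confidence interval of each treatment group". It then adds: "Missing values will be imputed using LOCF in the ANCOVA model".
- **SAP 2.5.2**, in the column giving the SAP's own method, reads "For continuous efficacy endpoint indicators, mixed model repeated measures (MMRM)/ANCOVA model was used to estimate the point estimate" and shortly afterwards "LOCF missing values will be used for imputation". It does not limit LOCF to the ANCOVA.

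**The concern.** Two things are wrong.

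First, 2.5.2 read literally puts LOCF into the MMRM for every continuous efficacy endpoint, whereas 5.2 and 6.5.1 together leave the MMRM unimputed. The 2.5.2 sentence stands in the column that describes the current SAP, so it is not superseded text.

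Second, LOCF suits this design poorly. Each cohort spends four weeks at each of three doses and reaches its target dose only on D57. A measurement from D57 or earlier therefore describes the starting or middle dose. Carried to D85, it is averaged with responses to 3.0, 4.5 or 6.0 mg and counted as one of them. The estimate for that dose is diluted if the effect grows with dose or time, and the interval is computed as if the filled value had been observed at D85. If missing data are concentrated in one cohort, the apparent dose-response changes as well.

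**Working it through.** **Planned size.** 3 cohorts × (8 + 4 + 2) = 42, which agrees with the plan. The documents give no SD, effect size or expected dropout, so the results below are in SD units or as shares.

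**Which carried values are lower-dose values** (Schedule of Activities, Table 3, protocol 7.3.2):

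- Lipids: scheduled laboratory visits on treatment are D15, D29, D57 and D85. A missing D85 value can only be filled from D57 or earlier among scheduled visits. D57 is the day of the first target dose.
- Fasting PD measures: D3, D8, D29, D57 (pre-dose), D78 and D85. A D78 value follows three target doses (D57, D64, D71). A lower-dose value is carried only if D78 is missing too.
- Blood pressure: vital signs are taken at every visit, before dosing. Values from D64 to D78 are on the target dose.

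**Observed at week 12** (Figs. S4, S8 and S7c):

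| Arm | Randomised | HOMA | Lipids | Blood pressure |
|---|---|---|---|---|
| 3.0 mg | 8 | 7 | 7 | 7 |
| 4.5 mg | 8 | 5 | 5 | 6 |
| 6.0 mg | 8 | 8 | 8 | 8 |
| Placebo | 12 | 11 | 10 | 11 |
| Dulaglutide | 6 | 6 | 6 | 6 |
| Total | 42 | 37 | 36 | 38 |

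For HOMA, 5/42 = 11.9% are missing overall, but 3/8 = 37.5% at 4.5 mg and 0/8 at 6.0 mg.

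**Dilution.** Let f be the fraction of the final effect already present in the carried value. The share of the arm's mean change that LOCF keeps is (observed + carried × f)/n. At 4.5 mg for HOMA this is (5 + 3f)/8:

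- f = 0: 5/8 = 62.5%
- f = 1/3: 6/8 = 75%
- f = 2/3: 7/8 = 87.5%
- f = 1: 100%

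The documents do not give f. The values 1/3 and 2/3 are the starting and middle doses as fractions of the target (1.5/4.5 and 3.0/4.5); they would apply if response were proportional to dose.

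**Interval width, 4.5 mg versus placebo.** The 90% half-width in SD units is t(0.95, df) × √(1/n₁ + 1/n₂), with df = N − 6 (five groups plus baseline) and the same residual SD throughout.

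- LOCF, 8 v 12, df 36: 0.771
- HOMA observed, 5 v 11, df 31: 0.914, so LOCF is 15.7% narrower
- Lipids observed, 5 v 10, df 30: 0.930, so LOCF is 17.1% narrower
- Blood pressure observed, 6 v 11, df 32: 0.860, so LOCF is 10.4% narrower

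**Joint effect.** An illustrative two-arm simulation (6,000 runs) took a true effect of −1 SD and a correlation of 0.7 between middle-dose and final values. Three of 8 active and 1 of 12 placebo values were carried, unrelated to outcome. LOCF gave −0.88 with coverage 0.896 at f = 2/3, and −0.76 with coverage 0.870 at f = 1/3. Observed cases gave −1.00 and −1.02, with coverage 0.90 in both. Simulation error in coverage is about √(0.9 × 0.1/6,000) = 0.004. Dilution is thus the main harm, and the coverage loss is small at this sample size.

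**The case against.** The strongest defence is about reach. The 6.5.2 ANCOVA is optional and its measures are secondary, exploratory or supportive. P-values are nominal, and the primary endpoints are safety and tolerability without formal testing. Figs. S4, S7 and S8 show reduced week-12 numbers, consistent with observed data, and the documents label no result as a LOCF ANCOVA. All of this stands and lowers the severity. It does not make LOCF a sound rule if the ANCOVA is run.

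Several stronger readings are tempting but not supported:

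- A reader might infer that 6.5.2 contradicts 5.2. It does not, because 5.2 allows stated exceptions. The conflict lies between 2.5.2 and the MMRM of 6.5.1 under the 5.2 default.
- A reader might infer that the HbA1c and fasting glucose results cannot be traced to a method. 6.5.1 names the model, and the note to Table S2 says the estimates come from an MMRM.
- A reader might take the three missing HOMA values as dropouts. At 4.5 mg, six patients have week-12 blood pressure and five have HOMA, so at least one patient without HOMA still contributed week-12 blood pressure.
- A reader might extend the 62.5% figure to the meal test. SAP 6.5.4 plans neither ANCOVA nor LOCF for it.
- A reader might quote a standard error 21% too small, from √(5/8) = 0.79. That applies to one arm's mean; the planned estimate is a contrast with pooled placebo.
- A reader might infer from 5.4 ("only the scheduled visit was used") that early-termination samples are discarded. Early termination has its own column in the Schedule of Activities, and nothing classes it as unscheduled.

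**Conclusion.** The concern holds in limited form. SAP 6.5.2 prescribes LOCF for a D85 analysis in which scheduled lipid values carried forward come from D57 or earlier. PD and blood pressure values do so when the patient has no later on-target measurement. SAP 2.5.2 also extends LOCF to the MMRM, against 5.2 and 6.5.1.

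For HOMA at 4.5 mg, LOCF would keep between 62.5% and 87.5% of the arm's mean change for f between 0 and 2/3. This assumes that all three missing values are carried from a lower dose; any carried from D78 would reduce the loss, and at f = 1 there is none. The share refers to that arm's own change. The bias in the contrast also depends on what is carried in the placebo arm. The interval for the contrast with placebo would be about 10% to 17% narrower across HOMA, lipids and blood pressure, assuming an unchanged residual SD. That narrowing is warranted only if carried values behave like D85 values.

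Severity is moderate. No displayed result is shown to depend on the rule.

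**What to change.** 1. In SAP 2.5.2, remove LOCF for endpoints analysed by MMRM, so that the table agrees with 5.2 and 6.5.1.
2. In SAP 6.5.2, replace the LOCF ANCOVA with the 6.5.1 MMRM and report the D85 contrasts. Every variable in that section is scheduled at D29, D57 and D85, and 6.5.1 already permits the model. Earlier values then inform D85 through the estimated correlation and do not stand in for it. The result rests on data being missing at random, which should be stated.
3. Keep LOCF, if at all, as a labelled sensitivity analysis.
4. Report the number observed at D85 in each arm beside every estimate.
5. Replace the open condition on running these models with a definite statement of which will be run.

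The cost is SAP wording and reuse of existing code. The downside is wider intervals in arms with missing data. With observed D85 data alone, the 4.5 mg versus placebo interval would be 12% (0.860/0.771, blood pressure) to 21% (0.930/0.771, lipids) wider than under LOCF. The MMRM may recover some of this from earlier visits.
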